## 6.5 Data analysis

Statistical analysis will be performed using the most recent version of SPSS (SPSS, Chicago, IL). PET and MRI scans will be co-registered and regions of interest (ROI) will be defined on anatomical structures outlined within the MRI scan. These ROI will be projected onto the  $[^{15}O]H_2O$  and  $[^{18}F]FDG$  scans, thus creating tissue-time activity curves. CBF and  $CMR_{glu}$  and glucose extraction fraction will be derived for these ROI using previously described methods [60, 96, 97]. In addition, CBF and  $CMR_{glu}$  will be calculated on a voxel-by-voxel basis using a basis function and a Patlak approach, respectively [98-102]. These functional images will be used for an analysis using SPM (statistical parametric mapping). The effects on the main and secondary outcomes will be analysed by routine tests for parametric and non-parametric comparison (analysis of variance and multiple regression modelling). A p-value of 0.05 will be considered statistically significant. A more detailed statistical analysis plan will be written prior to the completion of data collection.

## 7. STUDY MEDICATION

### 7.1 Storage and provision

Insulin detemir (Levemir®), NPH insulin (Insulatard®) and insulin aspart (NovoRapid®) will be stored in the in-hospital-pharmacy. The trial pharmacist will be responsible for ensuring that all study insulin is stored in a refrigerator, at 2-8 C, protected from exposure to any environmental changes and in a locked facility. Only the investigator and the trial pharmacist ('s assistant) will have access to the drug supplies.

### 7.2 Randomization of study medication

After review of their eligibility and final assessments, subjects will be randomized - by sequential randomisation - to the insulin to start with. The pharmacist will be responsible for randomization in this open-label study.

### 7.3 Dose titration

Patients will switch from their pre-trial basal insulin to the trial insulin on a unit-to-unit base if possible; when switching from detemir to NPH in case of large quantities, a 10% decrease in dose will be advised. Basal pre-dinner doses will be titrated to achieve target fasting blood glucose levels of 4-7 mmol/l, while avoiding hypoglycaemia. The following algorithm can be used as a guideline (SPC detemir); however, individual adjustments will be made:

| Mean self measured PG pre-breakfast | Dose adjustment (Levemir) |
|-------------------------------------|---------------------------|
| > 10,0 mmol/l (180 mg/dl)           | + 8                       |
| 9,1-10,0 mmol/ (163-180 mg/dl)      | + 6                       |
| 8,1-9,0 mmol/l (145-162 mg/dl)      | + 4                       |
| 7,1-8,0 mmol/l (127-144 mg/dl)      | + 2                       |
| 6,1-7,0 mmol/l (109-126 mg/dl)      | + 2                       |
| When self-measured PG is (once):    |                           |
| 3,1-4,0 mmol/l (56-72 mg/dl)        | - 2                       |
| < 3,1 mmol/l (< 56 mg/dl)           | - 4                       |

Patients are instructed carefully how to adjust their insulin dose and how to report their bloodglucose values to the research physician (by phone/ email). After dose adjustment, a nightly plasma glucose control at 3:00 am is advised. Dosing targets are not to be approached at the expense of causing problematic hypoglycaemia. The insulin aspart dose is initially not to be changed during the titration period, if possible. Titration is aimed to achieve post-meal glucoses of < 9 mmol/l. According to the investigator's judgement, doses can be individually adjusted.

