## 5.2. Protocol PET

After 12 weeks of treatment, patients will visit the Radionuclide Centre (RNC) in the early morning; they will be instructed to be in a fasting state and not to inject their prandial insulin.

Blood glucose values should be maintained at values ranging from 5-10 mmol/l. Therefore, blood glucose values will be checked (and adjusted, if necessary, by the infusion of 5% glucose) before and after testing using a finger prick.

[figure not shown]

All scans will be acquired at the same time of the day to minimise diurnal variations. All patients will receive an indwelling radial artery cannula. This arterial cannula will be inserted under local anaesthetics by an experienced clinician and will be used for blood sampling. In addition, a venous cannula will be inserted, which will be used for tracer injection (and glucose 5% if necessary). Subjects will be transferred to the scanning room and positioned on the scanner bed. They will be made comfortable in a supine position on the scanner table. The head will be fixated to reduce movement artefacts and, using laser beams, positioned within the centre of axial and transaxial field of views, such that the orbito-meatal line is parallel to the detectors.

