#### **Background**

As noted, 40 type1 diabetic patients will be randomly allocated to either insulin detemir or NPH insulin. They will use the trial insulin for a period of 12 weeks, after which they will switch to the other insulin. Participants will be contacted (by phone or email) to ascertain safety and tolerability, as well as compliance.

The **medication** used in the study, insulin detemir and NPH insulin, administered subcutaneously, are both registered for the treatment of diabetes mellitus for several years. Participants will be informed about the possible side effects, the most frequent side effect being, as for all insulins, hypoglycaemia. Less frequently occurring side effects are urticaria, rash, diabetic retinopathy, lipodystrophy, locally occurring hypersensitivity reactions, edema. The occurrence of hypoglycaemic episodes will be minimized by repeated instruction and contact with patients by the research physician, close monitoring of blood glucose levels and adjustment of the insulin dosing according to a previously described algorithm.

CSF will be obtained by a **lumbar puncture**. By using a very thin 25G atraumatic spinal needle, the risk of post-punctional headache is very small; patients will be informed about this potential risk and how to act in case this might happen.

Since **MRI** is a non-invasive procedure and no radioactivity is used, participants will not be at any risk during this test. Patients with claustrophobia will not be included in the study.

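### Section 7.3 sets a fasting target of 4-7 mmol/l, but its titration table raises the dose at 6.1-7.0 mmol/l, and the table names only one of the two study insulins

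*Protocol*

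**What the plan says.** Protocol section 7.3 (Dose titration) gives the fasting goal without naming an insulin: "Basal pre-dinner doses will be titrated to achieve target fasting blood glucose levels of 4-7 mmol/l, while avoiding hypoglycaemia". It then introduces a table: "The following algorithm can be used as a guideline (SPC detemir); however, individual adjustments will be made".

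The increases in the table depend on the mean self-measured pre-breakfast glucose. The lowest band that carries an increase is "6,1-7,0 mmol/l (109-126 mg/dl"), at +2. The decreases depend on a single reading. The band "3,1-4,0 mmol/l (56-72 mg/dl") carries -2, and anything below 3.1 mmol/l carries -4. The adjustment column is headed "Dose adjustment (Levemir"). No corresponding table is given for NPH, and nothing in the section says that this one applies to it.

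The same section says that patients are taught to adjust their own dose and to report their readings. It also says that targets should not be pursued at the cost of problematic hypoglycaemia, and it leaves room for discretion: "According to the investigator's judgement, doses can be individually adjusted". Appendix 3 (Background), after naming both insulins, lists among the means of keeping hypoglycaemia to a minimum the "adjustment of the insulin dosing according to a previously described algorithm".

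**The concern.** A goal and the rule meant to reach it should give the same answer for the same reading. Here they do not. A patient with a mean of 6.5 mmol/l has reached the goal by the sentence and is due an increase by the table. Two staff members, or one patient in two periods, could follow section 7.3 in good faith and act differently.

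Two things are at stake. First, Appendix 3 presents the algorithm as part of the protection against hypoglycaemia, so its lack of agreement with the target is more than a drafting blemish. Second, section 3.1 builds the hypothesis on similar glycaemic control under the two insulins. If the table guides the detemir period while judgement alone guides the NPH period, fasting glucose could differ because of how doses were titrated. The crossover would not remove such a difference, because it would travel with the treatment.

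**Working it through.** No sample-size or power formula applies. The check compares the glucose intervals.

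**Inputs, all from section 7.3**
- Stated fasting target: 4-7 mmol/l.
- Increases, by mean pre-breakfast value: +2 at 6.1-7.0, +2 at 7.1-8.0, +4 at 8.1-9.0, +6 at 9.1-10.0, +8 above 10.0.
- Decreases, by a single reading: -2 at 3.1-4.0, -4 below 3.1.

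**Step 1. Rule out a unit or transcription error.** Converting at 18.016 mg/dl per mmol/l:
- 6.1 × 18.016 = 109.9 and 7.0 × 18.016 = 126.1 (table: 109-126).
- 3.1 × 18.016 = 55.8 and 4.0 × 18.016 = 72.1 (table: 56-72).
- The bands at 7.1-8.0, 8.1-9.0 and 9.1-10.0 also agree to within about 1 mg/dl.

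Both unit columns give the same bands, so the 6.1-7.0 row is not a misprint in one of them.

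**Step 2. Read off the table's action for every on-target value.** In steps of 0.1, the range 4.0 to 7.0 has (7.0 - 4.0)/0.1 + 1 = 31 values.

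| Values (mmol/l) | Count | Text says | Table says |
|---|---|---|---|
| 4.0 | 1 | on target | -2 if measured once |
| 4.1-6.0 | 20 | on target | no change |
| 6.1-7.0 | 10 | on target | +2 as a mean |

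Check: 1 + 20 + 10 = 31. The table's no-change zone is 4.1-6.0, against a stated target of 4-7.

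**Step 3. Weigh the two ends.** The lower end is a shared boundary: a reading of exactly 4.0 belongs to both the target and the decrease band, and the decrease depends on one reading rather than a mean. The upper end is a conflict over a whole row. The rows on either side of 7.0 (6.1-7.0 and 7.1-8.0) carry the same +2, so the table gives the stated upper limit no role at all.

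**Step 4. Which insulin does the table cover?**
- Pointing to detemir only: the column heading, and the source given as the detemir SPC.
- Pointing to both: the 4-7 target is set for basal doses without naming an insulin, and Appendix 3 refers to the algorithm after describing both insulins.

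The document does not settle the question.

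**The case against.** The strongest defence is that the table does not bind. It may be used as a guideline, individual adjustment is expected, hypoglycaemia takes precedence over targets, and the investigator may depart from it. Nobody is therefore obliged to raise the dose of a patient at 6.5 mmol/l. This stands in part: the documents do not show that on-target patients will be up-titrated, only that the table calls for it where it is followed. It does not remove the conflict. Discretion settles individual cases but does not tell patients who self-adjust which of two upper limits to work to.

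On the second leg, NPH is not without rules. The target, the unit-for-unit switch, the night-time check and the post-meal aim are not confined to detemir, and section 7.3 has a specific provision for switching from detemir to NPH. This also stands. The heading is an ambiguity, and unequal titration is a possibility that the protocol leaves open, not something it prescribes. Glucose is also measured at both PET visits (Appendix 2), so a difference between treatments at the scan would be visible.

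A reader might go further and set the scan-day range in section 5.2 ("Blood glucose values should be maintained at values ranging from 5-10 mmol/l") against the fasting target, concluding that the statements cannot all be followed. The documents do not support that. The range is a condition for the scanning session, with its own correction by glucose infusion. It overlaps the target on 5-7 mmol/l, and values of 5.0-6.0 satisfy target, table and scan range together. A fasting value of 4.0-4.9 would be on target and below the scan range, but sections 5.2 and 5.3 provide for correcting it.

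**Conclusion.** Section 7.3 contradicts itself on when a basal dose should rise. The text's upper limit is 7 mmol/l, while the table's no-change zone ends at 6.0. Of the 31 on-target values, 10 carry an increase and one, the lower boundary, carries a decrease if measured once. This rests only on figures printed in the section.

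The 10 of 31 counts glucose values. A reader might infer that about a third of on-target patients would be up-titrated at each review. That would need an even spread of fasting means and mechanical use of the table, and the protocol supports neither.

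The detemir-only heading is a real but lesser point: it leaves the scope of the guideline open in an unblinded trial that presumes similar control. The documents do not show that titration will differ between periods, and no effect on CMRglu has been quantified. Sample size, power and alpha are untouched. The correction is worth making because the passage concerns the dosing of every participant and is cheap to repair.

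**What to change.** Amend section 7.3 in two places:

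1. Reconcile the stated fasting target with the table so that the table's no-change zone and the target are the same range, including which side the boundary value of 4.0 falls on. If a difference is intended, say so and explain it. The clinical team chooses the values.
2. State whether the guideline applies to both study insulins. If it does, change the column heading. If it does not, say what guides titration in the NPH period. Make the reference in Appendix 3 consistent with the answer.

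The cost is a wording amendment and an update to the patients' dosing instructions where they repeat the table. No visit, measurement or change to the sample size is needed, and sections 5.2 and 5.3 need no amendment on this account.

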### 8. STUDY DRUG DISCONTINUATION / WITHDRAWAL FROM THE STUDY

Study drug must be discontinued for a given patient if the investigator determines that continuing it would result in a significant safety risk for that patient. After the patient has entered the study, his treatment will be discontinued if one of or more of the following pertain(s):

- The occurrence of an adverse event or clinically significant laboratory change or abnormality that, in the judgment of the investigator, warrants discontinuation of treatment
- Patient's own decision
- Subjects need medical procedures that are not allowed in the protocol
- Subjects cannot undergo the procedures to investigate the research questions as outlined in this protocol

- Non-compliance
- In addition to these requirements for study drug discontinuation, the investigator should discontinue study drug for a given patient if, on balance, he thinks that continuation would be detrimental to the patient's well-being.

The physician can be guided by the criteria above, but may discontinue patients at any time based on her clinical judgment.

## 9. STUDY COMPLETION

The study will be considered completed for an individual patient when he completes both treatment phases, followed by the planned procedures. The study as a whole will be considered completed when all planned randomized patients have completed both treatment phases, followed by the final measurements.

## 10. LABORATORY PROCEDURES / TOTAL BLOOD VOLUME

Laboratory procedures will be performed at VUMC laboratories (Department of Clinical Chemistry and Endocrinology) and partly at Novo Nordisk A/S. Blood will be drawn during visit 1, 2, 3, 4, 5 and 6; for an overview see Appendix 1. During the study, 2 PET scans will be obtained, during which a maximum of 2x 250= 500 ml of blood will be drawn.

Maximal estimated blood volume to be obtained from 1 subject during the 24-week study period:

|                            |         |        |
|----------------------------|---------|--------|
| Screening (visit 1)        | approx. | 10 ml  |
| Visit 2                    |         | 3 ml   |
| Visit 4 & 6 : 2 x max. 200 |         | 400 ml |
| PET : 2x 250               |         | 500 ml |
| Total blood volume         |         | 913 ml |

## 11. INFORMED CONSENT FORM FOR TRIAL SUBJECTS

Prior to any trial related activity, the investigator will give oral and written information about the trial in a form that the subject can read and understand. The investigator must ensure the subject is fully informed about the aims of the trial, procedures, potential risks, any discomforts and expected benefits. The investigator must ensure the subject is informed and agrees that VUmc personnel, their representatives and possibly health authority (national or other) personnel can require access to the patient's data. It must be emphasized that participation is voluntary and that the patient has the right to withdraw from the trial at any time without prejudice. A voluntary, signed and dated Informed Consent will be obtained from the subject prior to any trial related procedure. The written informed

consent must be signed by the person who conducted the informed consent. In obtaining and documenting informed consent, the investigator must comply with the applicable local regulatory requirements and adhere to the ICH GCP guideline and the Declaration of Helsinki.

If information becomes available that may be relevant to the subject's willingness to continue participating in the trial, the investigator must inform the subject in a timely manner, and a revised written informed consent must be obtained.

Unexpected findings will be reported to the participant and to his general practitioner. If the participant does not want to be informed, he/she cannot participate in the trial.

A physician ([name], internal medicine, [contact]) who is not involved nor has any interest in the performance of the trial will be available; this person is knowledgeable about the protocol and can be consulted by subjects potentially interested in participation.

## **12. FINANCIAL COMPENSATION**

All subjects will receive a financial compensation for their participation and reimbursement for travelling expenses will be given based on prices of public transportation.

## **13. ETHICS**

The trial will be conducted in accordance with the Declaration of Helsinki for biomedical research involving human subjects and in accordance with the ICH guidelines for Good Clinical Practice.

## **14. PUBLICATION POLICY**

The investigator has the right to publish (including abstracts) the entire results of the study. Any scientific paper, presentation, communication or other information concerning this project must be submitted in writing to Novo Nordisk prior to submission for publication/presentation for comments. Novo Nordisk will respond within four weeks. All Intellectual Property created and provided by the Sponsor (Novo Nordisk) shall remain the sole property of the Sponsor. The Principal Investigator shall promptly disclose and assign to the Sponsor all inventions and discoveries made by the Principal Investigator related to the Trial. The Principal Investigator shall have a royalty-free right to use the results for non-commercial research and teaching purposes. Novo Nordisk shall have two weeks after receipt of any proposed publication, to object to such publication (or any communication) because there is patentable subject matter which needs protection and/or there is proprietary information of Novo Nordisk contained in the proposed publication. In the event of Novo Nordisk making an objection, the investigator shall refrain from making such publication for a maximum of three months from the date of receipt of the publication in order for Novo Nordisk to file patent application(s) with the applicable patent office(s).

The study will be the main part of a PhD project for one PhD student. A PhD-project has to fulfill the requirements of the Medical Schools at VU University, Amsterdam. In general, a PhD-thesis has to contain at least 5 chapters, consisting of manuscripts published in peer reviewed international journals. We expect that this study will yield sufficient data to meet these criteria.

Data will be presented at relevant national and international scientific meetings, including those from the Dutch Society for Diabetes Research, American Diabetes Association, European Association for Diabetes Research etc. Papers reporting data from the present study will be submitted to appropriate international scientific journals (depending on the results), including Diabetes, Diabetes Care, Diabetologia, Metabolism, Neurology etc.

## 15. INSURANCE

In case of possible damage as a result of participating in this research project, the loss is, in agreement with legal demands, covered by insurance. The address of the insurance company is:

Onderlinge Waarborgmaatschappij Centramed b.a.  
[name]  
[name]  
The Netherlands

In Dutch:

*Ingevolge art. 7 van de Wet medisch -wetenschappelijk onderzoek met mensen (Staatsblad 1998, 161) is door de verrichter van het onderzoek, het VUmc, een verzekering afgesloten die de door het onderzoek veroorzaakte schade door dood of letsel van de deelnemende proefpersonen dekt. Deze verzekering is afgesloten bij Onderlinge Waarborgmaatschappij Centramed b.a. , [name], [name]. De verzekeraar en de verzekering voldoen aan het besluit verplichte verzekering bij medisch-wetenschappelijk met mensen (Staatsblad 2003, 266) gestelde eisen. Aan het onderzoek deelnemende proefpersonen zullen schriftelijk worden geïnformeerd over de verzekering.*

## 16. ABBREVIATIONS

AD: Alzheimer's disease, AE: adverse event; AF: alkaline phosphatase, AGE: advanced glycation endproduct, ALAT: alanine-aminotransferase, ALE: advanced lipoxidation endproduct, ASAT: aspartate-aminotransferase, BMI: body mass index, CBF: cerebral blood flow, CEL: Nε-(carboxyethyl)-lysine, CML: Nε-(carboxymethyl)-lysine, CMR: cerebral metabolic rate, CNS: central nerve system, CSF: cerebrospinal fluid, 3DG: 3-deoxyglucose, DIR: double inversion recovery, DM: diabetes mellitus, DRP: diabetic retinopathy, DSP: diabetic sensorimotor polyneuropathy, FDG: fluorodeoxyglucose, FLAIR: fluid attenuating inversion recovery, fMRI: functional MRI; FOV: field of view; FWHM: full width half maximum;  $\gamma$ -GT:  $\gamma$ -glutamyl transferase, IL: interleukine, LAREB: Landelijke Registratie en Evaluatie Bijwerkingen (Netherlands Pharmacovigilance Centre); MBL: mannose-binding lectine; MCI: mild cognitive impairment, MDMA: 3,4-methylenedioxymethamphetamine, MPRAGE: magnetization prepared rapid acquisition gradient echo, MRI: magnetic resonance imaging, NPH: neutral protamine hagedorn, PET: positron emission tomography, ROI: region of interest, SAE: serious adverse event; SPM: statistical parametric mapping, SUSAR: suspected unexpected serious adverse reaction; TNF $\alpha$ : tumor necrosis factor  $\alpha$ .

## Appendix 1: Flow chart

| INcEREBRO                                                                  |                  |                    |           |              |            |                |            |              |            |            |
|----------------------------------------------------------------------------|------------------|--------------------|-----------|--------------|------------|----------------|------------|--------------|------------|------------|
| Flow Chart                                                                 | Visits           |                    |           |              |            |                |            |              |            |            |
|                                                                            | 1                | 2                  | TC1       | 3            | 4          |                | TC2        | 5            | 6          | E          |
|                                                                            | Screening        | Randomi-
sation | Tel call  | Measurements |            | Cross-
over | Tel call   | Measurements |            | Evaluation |
|                                                                            | Week
-4       | Week
0          | Week
2 | Week
12   | Week
12 |                | Week
14 | Week
24   | Week
24 | Week
26 |
|                                                                            |                  | Detemir            |           |              |            | NPH            |            |              |            |            |
|                                                                            |                  | NPH                |           |              |            | Detemir        |            |              |            |            |
| Informed Consent                                                           | X                |                    |           |              |            |                |            |              |            |            |
| Incl./Excl. Criteria/ demography                                           | X                |                    |           |              |            |                |            |              |            |            |
| Start of study insulin                                                     |                  | X                  |           |              |            | X              |            |              |            |            |
| Insulin Therapy (titration,
monitoring hypoglycaemic events
etc)     | X                | X                  | X         | X            | X          |                | X          | X            | X          | X          |
| Patient History
- past
- recent                                      | X                | X                  | X         | X            | X          |                | X          | X            | X          |            |
| Physical Examination
- General
- DSP
- Ewing test
- Fundoscopy | X
X
X
X |                    |           | X            |            |                |            | X            |            |            |
| Vital Signs (incl. body wt)                                                | X                | X                  |           | X            | X          |                |            | X            | X          | X          |
| Monitoring (S) AE's                                                        |                  |                    | X         | X            | X          |                | X          | X            | X          |            |
| Concomitant medication                                                     | X                | X                  | X         | X            | X          |                | X          | X            | X          | X          |
| PET-scan                                                                   |                  |                    |           | X            |            |                |            | X            |            |            |
| fMRI-scan                                                                  |                  |                    |           |              | X          |                |            |              | X          |            |
| Blood measurements
- screening
- study parameters                    | X                | X                  |           | X            | X          |                |            | X            | X          |            |
| Lumbar puncture                                                            |                  |                    |           |              | X          |                |            |              | X          |            |
| Questionnaires:
EDI-II; CES-D
POMS, Likert
DEBQ                   | X                | X                  |           | X
X       | X          |                |            | X
X       | X          |            |
| Urine analysis                                                             |                  | X                  |           | X            |            |                |            | X            |            |            |

